The first phase of the intervention component will consist of a pilot phase in which our AI algorithms for predicting treatment changes and prognosis are incorporated into the MatchMiner “patients for clinical trials” workflow. Specifically, filters already generated by the MatchMiner team to identify patients who may be candidates for specific clinical trials based on NGS data will be cross-referenced with predictions of new treatment and prognosis that are generated each time a patient has an imaging report generated for cancer reassessment. This combined information will be used to sort the list of filter patients by propensity to change treatment as well as timing of most recent progression and brain metastasis. These sorted MatchMiner lists will then be delivered as spreadsheets to collaborating investigators in the Center for Cancer Therapeutic Innovation, the Breast Oncology Center, and the Thoracic Oncology Program, and qualitative feedback will be solicited regarding steps to improve our modeling and/or delivery of information. Feedback will be collected via a structured SurveyMonkey survey every six months and informally via meetings with these disease centers. These collaborators are co-investigators on our protocol, not research subjects. Survey questions will ask respondents to provide their disease center; role (MD, RN NP/PA, other); estimates of how often they review trial readiness spreadsheets; estimates of the extent to which the readiness spreadsheets have been incorporated into disease center team workflows; estimates of the subjective accuracy of trial readiness predictions; estimates of whether patients have consented to trials or enrolled on trials specifically because of these predictions; feature requests; any ethical concerns; and whether readiness spreadsheets are being used in disease centers for any purposes other than identifying patients for clinical trials (eg maintaining disease center databases, identifying patients who may need palliative care services). CCTI will also review each ‘ready’ patient in our spreadsheets to indicate whether a patient was indeed discussed with the treating clinician for possible referral to CCTI; and if not, why not.

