The second phase of the intervention component will consist of a pragmatic, prospective, randomized health care system process implementation study. This is not a clinical trial by the NIH definition, since the outcomes assessed will be operational rather than patient-level behavioral or health-related outcomes.

The intervention procedure for this second phase will be:

- On the study go-live date, which is currently anticipated to be January 2, 2023 but may be adjusted if needed based on technical factors identified during the pilot phase, we will identify all patients with OncoPanel results (who therefore have data accessible through MatchMiner already), who are still alive at that date, whose tumor NGS included any OncoTree code other than leukemia, lymphoma, myeloma, or MDS codes; and who are age 18 or over on that date.

261

262 • Such patients will be randomly divided into three groups; randomization will be  
263 performed at the patient level. For Group 1, MatchMiner will operate as it has previously;  
264 clinicians can use the software to identify potential trials for their patients based on NGS  
265 data, and clinical trial investigators can use it to identify potential patients for their trials.  
266 For Group 2, MatchMiner will continue to operate as before, but additionally, email  
267 notifications containing MatchMiner information will be automatically sent to treating  
268 oncologists each time a patient is clinical trial “ready” (has a predicted probability of  
269 treatment change that falls above the best F1 cutoff threshold for this prediction as  
270 evaluated in the retrospective validation set, also has MatchMiner trial matches for trials  
271 on which the patient has not previously enrolled, and has not triggered a recent  
272 “readiness” email to the treating clinician). For Group 3, MatchMiner will still continue  
273 to operate as before, with NGS-based matches available to all treating oncologists and  
274 trial investigators, and additionally, lists of “ready” patients will be generated based on  
275 AI model results as in Group 2; however, these lists will be manually reviewed by the  
276 study team and cross-referenced with manual medical record review before the  
277 MatchMiner notifications are emailed to treating oncologists. Manual review criteria for  
278 proceeding with each email will include evaluation of whether patients have already been  

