279 referred to hospice or are being treated with comfort measures only at the time of the last  
280 imaging report; whether patients have documented performance status of 3-4; and  
281 whether patients are obviously ineligible for all trials provided in the MatchMiner report  
282 as evaluable in the medical record based on trial-specific eligibility criteria. There will be  
283 no direct contact with patients in this study.

284

285 • We have collected preliminary data to inform the randomization and analysis strategy. As  
286 of February 2022, there were 46,097 patients with tumor NGS (OncoPanel) data..  
287 However, this includes both living and deceased patients, patients with hematologic  
288 malignancies who will not be included in this study, and patients not actively following at  
289 DFCI. We therefore examined our AI algorithm development data from 2019 (to exclude  
290 COVID-related variability in trial accrual). We estimate that there were 11,650 patients  
291 who had NGS data and who had any imaging studies from January 1, 2019 through  
292 October 31, 2019. Of these patients, approximately 890 (7.6%) enrolled in a therapeutic  
293 clinical trial between January 1, 2019 and November 30, 2019. If we perform 1:1:1  
294 randomization for all living patients with NGS and given growth in the PROFILE cohort  
295 since 2019, we will therefore have approximately 3800 patients in each group who have  
296 imaging studies during our ten-month intervention period. Stratified randomization will  
297 not be performed, due to the large sample size and heterogeneity in treating disease  
298 centers, treating clinicians, cancer types. Clinicians will be given the opportunity to opt  
299 out of ongoing emails from the study in general, or for individual patients, at any time.  
300 Patients whose clinicians opt out of notifications will remain in their assigned group for  
301 analysis; that is, the primary analysis will follow an intention to treat approach.

302 The primary study outcome will be whether patients enroll on any DFCI therapeutic  
303 clinical trial of an anti-cancer systemic therapy during the intervention follow-up period.  
304 This period will be defined as follows. Beginning in December 2023, total trial

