enrollment events across all three study arms will be quantified every two months, without comparing enrollment among arms; the goal of this procedure is to ensure adequate statistical power to compare among arms. Once total trial enrollment reaches 1000 patients, or the follow-up period reaches July 1, 2024, the study will be discontinued and outcomes by arm assessed. Trial enrollment will be ascertained using structured institutional data via an existing data feed from the Dana-Farber Enterprise Data Warehouse to the MatchMiner team. In our primary analysis, we will pool the two AI-assisted intervention arms and compare trial enrollment rates in the AI-assisted group (N~7600 total) to the standard process arm (N~3500) using a simple two-sample Z test of proportions. If the standard process arm enrollment rate remains ~ 7.5%, we would have 80% power given two-sided  $\alpha=0.05$  to detect an increase in enrollment rate to 9.1%. This would represent an operationally meaningful 21% relative increase in enrollment rates. We will take this approach rather than a time-to-event analysis, since traditional right censoring, in which patients are lost to follow-up but undetected events might have occurred after they were no longer followed, is not relevant for this outcome; we will have complete data on the outcome from DFCI (unascertained enrollment in a therapeutic trial would not be possible).

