Comparison of the two intervention arms (Groups 2 and 3) to each other and to Group 1 will be a pre-specified secondary analysis. Additional pre-specified secondary outcomes will include whether patients have any consultations in the Center for Cancer Therapeutic Innovation and whether they consent to any therapeutic trial. Further pre-specified secondary outcomes will include trial consent and enrollment rates among patients who at any point during follow-up were ascertained as likely to change treatment in the next 30 days as defined by our algorithm; the proportion of new systemic therapy regimens that were clinical trials; and clinician opt-out rates. Of note, these are administrative/process outcomes, not clinical outcomes, such that our intervention does not itself constitute a clinical trial by the NIH definition. These endpoints will also be analyzed using the MatchMiner EDW data feed. Furthermore, the intervention consists of comparing ways to deliver information from the MatchMiner tool that is already accessible to treating clinicians, such that there is minimal risk to patients and clinicians.

The pilot phase work will be downsized when the interventional phase begins to minimize impact of the pilot on evaluation of the intervention. Specifically, the Breast Oncology Center and Thoracic Oncology Program components of the pilot will be discontinued, and the trials involved in the Center for Cancer Therapeutic Innovation (CCTI) pilot will be restricted to a subset of trials for rare patient populations for which CCTI collaborators determine there is a strong need to identify as many potential patients as possible. This list of trials will be determined at the time of intervention go-live, since it is challenging to predict trial portfolios far in advance.

This will be an interventional research study, but it will not itself constitute a clinical trial by the NIH definition, since the outcomes being measured (whether patients consent to or enroll on therapeutic clinical trials) are not themselves health-related outcomes for the patient.

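### The secondary analysis of patients flagged as likely to change treatment does not limit the count to consents and enrollments after the flag

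*Protocol*

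**What the plan says.** All of this is in Protocol section 9.0, second phase of the intervention component.

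- **The subset.** One secondary outcome is "trial consent and enrollment rates among patients who at any point during follow-up were ascertained as likely to change treatment in the next 30 days". The algorithm supplies this flag. No start date is attached to the outcome.
- **The window.** Enrollment is defined for the primary outcome as enrollment on a "clinical trial of an anti-cancer systemic therapy during the intervention follow-up period". The end is set by this rule: "Once total trial enrollment reaches 1000 patients, or the follow-up period reaches July 1, 2024, the study will be discontinued and outcomes by arm assessed". Section 8.0 words the end of the window differently, but that too is a calendar window and not one tied to the flag.
- **The method.** For the primary comparison the protocol says "We will take this approach rather than a time-to-event analysis".
- **When emails go out.** In Group 2, "notifications containing MatchMiner information will be automatically sent to treating" clinicians once a patient is trial-ready. That status needs a score above the best-F1 cutoff, no recent readiness email, and a further condition: the patient "also has MatchMiner trial matches for trials" not previously joined. Group 3 adds manual review before the email.
- **When scores are produced.** The pilot description speaks of "predictions of new treatment and prognosis that are generated each time a patient has an imaging report generated for cancer reassessment".

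**The concern.** The subset is defined by something that happens during follow-up, while the outcome is counted from the start of follow-up. Take a patient who enrolls in month 2 and is first flagged in month 8. That patient enters the subset because of the month-8 flag and brings along the month-2 enrollment as a success. An email is sent only once the patient has been flagged, so the month-2 enrollment cannot be a result of the intervention on that patient.

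Of the listed secondary outcomes, this one comes closest to the patients whom the emails can reach. A reader will take its rate as the rate of trial uptake once the algorithm says a change of treatment is near. As worded, it is a mixture of uptake before and after that moment, and the contrast between arms is measured against a background of events that the intervention could not have influenced.

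**Working it through.** **1. The plan's own figure.** The protocol gives no power for this secondary analysis, so the primary power statement serves as a check of the formula. Inputs (section 9.0): 3500 standard and 7600 AI-assisted patients, 7.5% versus 9.1%, two-sided 0.05, two-sample Z test.

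Power = Φ[(d − 1.96·SE0)/SE1], with SE0 from the pooled rate and SE1 from the two separate rates.

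d = 0.016, SE0 = 0.00573, SE1 = 0.00554, so Φ[(0.016 − 0.01122)/0.00554] = Φ(0.862) = 80.6%. The stated 80% is reproduced. With the 3800 patients per group given earlier in the section, it is 82.8%.

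**2. Effect on the rate and the ratio.** Let q be the control rate as worded and s the share of those enrollments that precede the first flag. Both are assumptions. Suppose the intervention multiplies only post-flag enrollment, by 1.21 (the protocol's relative effect). Then:

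- Ratio as worded = s + (1 − s)·1.21, which is 1.19, 1.17, 1.15 and 1.105 for s = 10%, 20%, 30% and 50%.
- Control rate after the flag, among those not yet enrolled = q(1 − s)/(1 − qs). With q = 15% and s = 20% this is 0.12/0.97 = 12.4%, against 15.0% as worded.
- Risk difference in that case: as worded 17.5% − 15.0% = 2.5 points; from the flag 15.0% − 12.4% = 2.6 points. The difference hardly moves; the rate and the ratio do.
- Power in that case if 30% of imaged patients are flagged (1140 versus 2280): 46% as worded, 53% counted from the flag.

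**3. Effect on power at a fixed absolute effect.** The flagged share is applied to 3800 and 7600. The control rate as worded is the post-flag rate divided by (1 − s), and the absolute effect is unchanged.

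- Scenario A (assumed): 40% flagged, 1520 versus 3040; post-flag 10% versus 13%.
- Scenario B (assumed): 30% flagged, 1140 versus 2280; the whole primary effect of 1.6 points arises in this subset, so 1.6/0.30 = 5.3 points, 12.0% versus 17.3%.

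| Pre-flag share s | A: control rate as worded | A: power | B: control rate as worded | B: power |
|---|---|---|---|---|
| 0 (post-flag count) | 10.0% | 84.6% | 12.0% | 98.6% |
| 10% | 11.1% | 81.6% | 13.3% | 97.9% |
| 20% | 12.5% | 78.1% | 15.0% | 97.0% |
| 30% | 14.3% | 74.0% | 17.1% | 95.6% |
| 40% | 16.7% | 69.2% | 20.0% | 93.7% |

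For s of 20% to 40% the loss is about 6 to 15 points in A and 2 to 5 points in B. The post-flag row keeps all flagged patients in the denominator. Removing those already enrolled changes its power by less than half a point (A at s = 40%: 84.9%).

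**4. Plausibility limit.** The whole of Group 1 should yield about 7.5% × 3800 = 285 enrollments. Scenario A at s = 40% puts 16.7% × 1520 ≈ 253 of them, or 89%, in the flagged 40%. That is possible but close to the edge, so the largest losses are upper illustrations.

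**The case against.** **The protocol does not say that pre-flag enrollments count.** It does not. It names a subset and two rates in one clause, and the whole-follow-up window is stated for the primary outcome. An index date could be set in an analysis plan that is not shown. This stands in part: the point is that the text fails to exclude such events. But the protocol does fix membership at any time in follow-up, and the only windows it gives run over calendar time, so the natural reading counts them.

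**The comparison between arms is valid as worded.** This stands fully. A reader might infer a bias between arms from a subset formed after randomization. If the score is run alike in all arms, the first flag precedes any study email about that patient, so flagged status and pre-flag enrollments balance by randomization.

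**The gain is modest and rests on assumed inputs.** This also stands. A reader might set the 98.6% in scenario B against the 80.6% to 82.8% for the whole cohort and credit the gap to counting from the flag. That contrast is between a subset and the full cohort; the wording as it is already gives 93.7% to 97.0% there. Nor do the documents support the idea that being on a trial leads to more scans and so to more flags.

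**The subset is wider than the email trigger by choice.** A reader might call it an error that patients without a MatchMiner match are included. Trial uptake among all patients likely to change treatment is a legitimate operational question. Restricting to matched patients answers a different question and is not a correction.

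**Conclusion.** The point holds as a cheap improvement to one secondary analysis. As worded, the analysis admits enrollments and consents that came before the first flag. These overstate the rate after a flag, pull the ratio toward 1 and cost some power. There is no bias between arms, the primary analysis is unaffected, and the documents do not support a claim that a real effect would be hidden.

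The size cannot be derived from the protocol. With assumed pre-flag shares of 20% to 40%, the loss of power runs from about 2 to 15 points across the two scenarios; with no pre-flag enrollments there is none. The conclusion assumes that the score is run in the same way in all three groups, that flagging in this outcome uses the same cutoff as the email trigger, and that scores are produced at imaging reports in the randomized phase as in the pilot.

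**What to change.** - In all three arms, define the index date as the first imaging report in follow-up at which the treatment-change score exceeds the cutoff. Compute it silently in Group 1 and before manual review in Group 3, so that it precedes any email in every arm.
- Count only consents and enrollments after that date.
- State whether patients already enrolled at the index date stay in the denominator, with only new enrollments counted. Either choice is balanced between arms and makes little difference to power.
- Optionally, add a sensitivity analysis limited to patients who also meet the MatchMiner-match condition of the email trigger, computed the same way in all arms.

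The cost is a sentence or two of wording, a small programming task to store the score dates (and, for the sensitivity analysis, the matches) in Group 1, and fewer counted events. No ranking of the secondary analyses is needed.

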**10.0 Data and Specimen Banking**

Not applicable

**11.0 Data Management and Confidentiality**

This is a medical record analysis and health system process implementation study; it does not involve direct patient contact, and the research could not be done if contacting all ~60,000 patients for algorithm development and implementation were required. Furthermore, the implementation component of our study in MatchMiner addresses operational outcomes rather than biomedical patient-level outcomes; it similarly involves no patient contact. The medical risk to patients will be minimal, since their clinicians will continue to make all relevant standard-of-care treatment or therapeutic clinical trial recommendations. As such, a waiver of informed consent will be requested. The principal theoretical risk in the medical records review component of the study is loss of confidentiality. All structured and unstructured data obtained through OncDRS for this study will be stored only in secure password-protected DFCI-approved storage locations, limited to Google Cloud Storage (per a Business Associate Agreement between DFCI Clinical Informatics and Google to provide HIPAA-compliant data storage), Partners DropBox, DFCI Redcap, or servers housed in the DFCI Department of Data Sciences. Only study investigators will have access to the data.

**12.0 Provisions to Monitor the Data to Ensure the Safety of Subjects**

Not applicable

**13.0 Withdrawal of Subjects**

Not applicable

**14.0 Risks to Subjects**

As above, this will be a medical record algorithm development and operational process research study without patient contact; as such a waiver of informed consent will be requested. The principal theoretical risk in any medical records review study is loss of confidentiality, which will be addressed using the measures in Section 11 above.

**15.0 Potential Benefits to Subjects**

This project does not include a direct benefit for subjects included in the analysis.

**16.0 Vulnerable Populations**

Not applicable

**17.0 Community-Based Participatory Research**

Not applicable

**18.0 Sharing of Results with Subjects**

Not applicable

**19.0 Setting**

This is a medical record analysis project using Dana-Farber Cancer Institute data files and an operational process study to be conducted at Dana-Farber Cancer Institute.

## **20.0 Resources Available**

The Population Sciences Division maintains its own server infrastructure and systems administration staff that provide data storage, data backup, and data security in support of large data analysis projects. The servers are configured as a virtual server pool with virtual server hosts connected to a centralized Storage Area Network (SAN) device. Server virtualization increases the efficiency and flexibility of the server pool while minimizing downtime and cost. The server pool currently has 20 processor cores and a data storage capacity of 9 terabytes. This server infrastructure has a dedicated Systems Administrator to optimize performance, maintain security patches, perform backups, and execute other related tasks. Researchers in the Division have access to additional resources through the Research Computing group. Research Computing provides a variety of services including file server space, backup services, website hosting, and support of some workstation computers.

## **21.0 Prior Approvals**

Not applicable

## **22.0 Recruitment Methods**

Not applicable

## **23.0 Local Number of Subjects**

Not applicable

## **24.0 Provisions to Protect the Privacy Interests of Subjects**

There will be no direct patient contact in this study. The algorithm development study includes a Combined *retrospective* review with *prospective* OncDRS data refreshes. The OncDRS refreshes will allow us to update the cohort over time. Therefore, we recognize that not every piece of data for this project is on the shelf as of today. However, every piece of data will ONLY be utilized via medical record review and OncDRS refreshes. There will be NO direct patient interaction during this project. The principal theoretical risk in any medical records review study is loss of confidentiality. The data obtained for this study will be stored in DFCI-approved server locations, accessible only to study staff, as described above. In the implementation component of the study, filtered MatchMiner results are being delivered to collaborators in disease centers who are also investigators on this protocol; prospective notifications to treating oncologists will be delivered using the MGB email system as is other patient-related information.

